## Abstract

**Background:**

The access to and uptake of evidence-based behavioral parent training for children with behavioral difficulties (i.e., oppositional, defiant, aggressive, hyperactive, impulsive, and inattentive behavior) are currently limited because of a scarcity of certified therapists and long waiting lists. These problems are in part due to the long and sometimes perceived as rigid nature of most evidence-based programs and result in few families starting behavioral parent training and high dropout rates. Brief and individually tailored parenting interventions may reduce these problems and make behavioral parent training more accessible. This protocol paper describes a two-arm, multi-center, randomized controlled trial on the short- and longer-term effectiveness and cost-effectiveness of a brief, individually tailored behavioral parent training program for children with behavioral difficulties.

**Methods:**

Parents of children aged 2–12 years referred to a child mental healthcare center are randomized to (i) three sessions of behavioral parent training with optional booster sessions or (ii) care as usual. To evaluate effectiveness, our primary outcome is the mean severity of five daily ratings by parents of four selected behavioral difficulties. Secondary outcomes include measures of parent and child behavior, well-being, and parent–child interaction. We explore whether child and parent characteristics moderate intervention effects. To evaluate cost-effectiveness, the use and costs of mental healthcare and utilities are measured. Finally, parents’ and therapists’ satisfaction with the brief program are explored. Measurements take place at baseline (T0), one week after the brief parent training, or eight weeks after baseline (in case of care as usual) (T1), and six months (T2) and twelve months (T3) after T1.

**Discussion:**

The results of this trial could have meaningful societal implications for children with behavioral difficulties and their parents. If we find the brief behavioral parent training to be more (cost-)effective than care as usual, it could be used in clinical practice to make parent training more accessible.

**Trial registration:**

The trial is prospectively registered at ClinicalTrials.gov (NCT05591820) on October 24th, 2022 and updated throughout the trial.

**Supplementary Information:**

The online version contains supplementary material available at 10.1186/s12888-024-05649-8.

## Background

Behavioral difficulties, including oppositional, defiant, aggressive, hyperactive, impulsive, and inattentive behavior, are one of the most common reasons for referral to mental healthcare among children and adolescents [1, 2]. When left untreated, problems may exacerbate and put children at risk of adverse outcomes later on in life, such as school dropout, delinquency, substance use and depression [3, 4]. Ideally, treatment should prevent this escalation of problems, reduce the need for long and intensive treatments, and lower societal costs [5]. Behavioral parent training is the first psychosocial treatment of choice for reducing behavioral difficulties in preschool and school aged children [6–12]. However, its use in clinical practice is limited by a scarcity of certified therapists, long waiting lists, and the typically long and sometimes perceived as rigid nature of behavioral parent training programs, which may lead to parents not starting or finishing behavioral parent training [13–15]. To reduce these barriers, this study evaluates a brief and individually tailored behavioral parent training program for children with behavioral difficulties (the “*PAINT-GGZ*” program, developed by the Psychosocial ADHD & disruptive behavior INTerventions [PAINT] consortium). The brief training includes optional booster sessions for families who need additional support [16].

In behavioral parent training, parents are taught techniques to curtail children’s behavioral difficulties by avoiding or breaking coercive parent–child interactions [17]. Parenting programs have moderate short-term effects on child conduct problems [18], oppositional behavior [19, 20], inattentive and hyperactive/impulsive behavior [21, 22], and parenting [23]. The longer-term effects of behavioral parent training are less consistent: A meta-analysis on behavioral parent training for children with attention deficit/hyperactivity disorder (ADHD) found mostly sustained effects five months to one year after the intervention [24], while a meta-analysis on behavioral parent training for children with disruptive behaviors (e.g., tantrums, arguing, rule-breaking) shows a large heterogeneity in results, with some studies showing sustained effects and other studies showing fade-out effects or sleeper effects three years after the intervention [25]. Overall, the evidence base of behavioral parent training is well-established.

However, a scarcity of certified therapists, long waiting lists, and the typically long and sometimes perceived as rigid nature of behavioral parent training programs undermine the use of parenting interventions in clinical practice. That is, only a minority of families who seek treatment actually receive parent training, because there is a lack of certified therapists who can provide behavioral parent training and waiting lists for parenting interventions are common [15]. Also, clinicians sometimes do not recommend parent training, but rather redirect children towards medication [26]. Additionally, behavioral parent training programs are typically long (8 to 12 sessions [14],) and generally not tailored to the specific behavioral difficulties that parents seek help for [27]. This is problematic, as behavioral parent training programs are more likely to be effective when their content is tailored to the specific problems parents encounter in daily life [14]. The perceived rigidity and length of programs may lead to parents not starting or completing behavioral parent training [15, 28]. That is, at least 25% of parents who are eligible to participate in scientific studies and qualify for behavioral parent training do not enroll in a parenting program and another 26% terminate the training prematurely [13]. Brief and individually tailored behavioral parent training programs may reduce these problems, but the few existing brief programs are barely provided and mainly evaluated in prevention settings [29, 30]. There is thus an urgent need for evidence-based, brief and individually tailored programs.

To address this need, this randomized controlled trial evaluates the effectiveness of a brief and individually tailored behavioral parent training program with optional booster sessions for children with behavioral difficulties. The program is based on intervention elements that were effective in reducing children’s behavioral difficulties in the broader literature and our earlier work: antecedent techniques (i.e., stimulus control techniques) and consequent techniques (i.e., contingency management techniques) [22, 31, 32]. Antecedent techniques are aimed at changing child behavior by manipulating the antecedents of this behavior (e.g., by setting clear rules and providing structure) and consequent behavioral techniques are aimed at changing child behavior by manipulating their consequences (e.g., by praising desired behavior and ignoring undesired behavior). In a recent microtrial in which we evaluated the efficacy of antecedent and consequent techniques, both sets of techniques were found to reduce behavioral problems of children with ADHD in brief (i.e., two sessions) behavioral parent training, of which antecedent techniques were especially effective in decreasing inattention [33]. This microtrial also showed that the magnitude of effects of a brief program (i.e., medium-sized effects) was similar to those of traditional, longer programs on reducing child behavioral difficulties [23, 33, 34].

Building upon the findings of our microtrial, the brief behavioral parent training of the present trial consists of two sessions in which antecedent and consequent techniques are combined and a third session aimed at the evaluation and maintenance of applying the learned techniques. To prevent relapse and the possible use of other, more intensive and expensive treatments, parents can receive booster sessions in the first year after the brief training. Similar to the microtrial, the behavioral parent training is individually tailored by letting parents select four target behaviors they want to address in the training and by creating an individually tailored intervention plan based on the functional analysis (see [33]). A non-randomized pilot study (*N* = 28) preceding the present trial indicated a relatively low dropout rate (14.2%), high treatment feasibility and parent and clinician satisfaction, and a reduction of children’s behavioral difficulties from pre to post intervention [35].

### Objectives and hypotheses

The first objective of this study is to examine the short- and longer-term (i.e., one year) effectiveness of the brief and individually tailored behavioral parent training program with optional booster sessions compared to care as usual (CAU) on daily measured child behavioral difficulties (primary outcome) and on a range of secondary outcomes (see Outcomes). Additionally, we will explore whether a number of general demographic and clinical characteristics, parental attachment, parental psychopathology, parental reward responsivity, and reward and punishment sensitivity of the child moderate the short- and longer-term intervention effects on our primary outcome. The second objective is to investigate the cost-effectiveness of the program compared to CAU. As we assess cost-effectiveness based on measures at baseline and one year after the intervention, we can only draw conclusions about the cost-effectiveness on the longer term.

Based on our earlier work [33, 35], we hypothesize that the brief behavioral parent training with booster sessions will be more effective than CAU in reducing children’s behavioral difficulties. Consequently, we expect parents who receive the brief behavioral parent training to use less subsequent care and thus hypothesize the brief training to be more cost-effective than CAU on the longer term.

## Methods

### Study design

In this two-arm multi-center randomized controlled trial, parents of children who experience behavioral difficulties in the home setting and were referred to a child mental healthcare center, are randomly assigned (1:1 ratio) to either (a) three sessions of brief behavioral parent training with optional booster sessions, or (b) CAU, as regularly provided by the involved mental healthcare centers. There are no restrictions regarding the type (e.g., psychoeducation, parent counseling and support, individual child therapy, medication) or duration of CAU, only the brief parent training investigated in this trial is not allowed. Both parents and children in the brief behavioral parent training group are not allowed to receive CAU until the first posttreatment assessment (T1). After that, CAU is allowed and parents can also make use of booster sessions with the therapist who provided the training.

### Study setting

To ensure our findings reflect the real-world impact of brief behavioral parent training (i.e., to test effectiveness rather than efficacy), the trial is fully embedded in routine mental healthcare. The participating centers are academic and non-academic youth mental healthcare centers of various sizes. Therapists who provide the brief behavioral parent training have a master’s degree in psychology or child, family and education studies and have had postmaster education in cognitive behavioral therapy (at least 50 h) or have a registered higher vocational education degree as social worker in cognitive behavioral therapy. The therapists are trained in the brief parent training by supervisors qualified in cognitive behavior therapy during a one-day training of seven hours, in which therapists practice the parent training by roleplay and evaluate on their performance. Therapists also receive weekly supervision by these qualified supervisors when providing the brief parent training. Additionally, the supervisors provide feedback to each therapist on the audio-taped first session regarding protocol fidelity, intervention integrity, and the process of providing the training (e.g., engaging parents, didactic skills). There are no in- or exclusion criteria for clinicians in the CAU condition. To prevent contamination of the two research arms, therapists never provide both the brief behavioral parent training and CAU to parents participating in this study and are instructed not to share information about the contents of the brief training.

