##### Use of healthcare

Use of mental healthcare within the organization where the child is treated is measured by drawing up an inventory (based on patient records) of the type of care (brief behavioral parent training, booster sessions, CAU) that is used and the duration (in minutes) of this care between T0 and T3 in both arms. The broader use of healthcare within and outside the mental healthcare centers is assessed with the *Vragenlijst Intensieve Jeugdzorg*, a Dutch questionnaire on intensive youth care [60]. This questionnaire assesses the use of a wide variety of healthcare (e.g., contact with general practitioner or medical professionals, use of social services or (alternative) medicines), along with the child’s use of education, contact with judicial authorities, and losses in the productivity of parents. Parents complete this questionnaire about the use and intensity of healthcare of both the child and themselves in the past three months. This outcome is measured at T0 and T3. Both measures of healthcare use (i.e., inventory of care and questionnaire) will be combined to obtain a complete image of all used care.

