##### Costs of healthcare

Healthcare costs are estimated from a societal perspective [5]. Costs of mental healthcare are estimated by multiplying the used care by the reference prices provided in the Cost Manual of the Dutch National Health Care Institute. Costs of medication are estimated by using prices provided by the Dutch National Health Care Institute [61]. Costs in other sectors (e.g., education, justice) are estimated by using reference prices provided in the Manual Intersectoral Costs and Benefits [62]. All costs are estimated after families’ participation in the study, when their healthcare use is fully measured.

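### The stated costing rule has no item for the training day, weekly supervision and tape feedback with which the brief training is delivered, so the ICER may understate that arm's cost

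*Protocol article*

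**What the plan says.** Protocol article, Study setting, describes three supports for therapists who give the brief training. They are taught the programme "during a one-day training of seven hours". While delivering it, "Therapists also receive weekly supervision by these qualified supervisors when providing the brief parent training". In addition, "the supervisors provide feedback to each therapist on the audio-taped first session". Of the comparator the section says "There are no in- or exclusion criteria for clinicians in the CAU condition"; it does not say whether those clinicians receive training or supervision. The section presents the trial as embedded in routine care in order "to test effectiveness rather than efficacy".

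Use of healthcare sets out how resources are counted. Patient records supply the type of care and "the duration (in minutes) of this care between T0 and T3 in both arms", and a parent questionnaire supplies wider use by child and parents. Costs of healthcare adopts a societal perspective and states the valuation rule: "Costs of mental healthcare are estimated by multiplying the used care by the reference prices". Statistical analysis puts the resulting costs into the ICER for QALYs, the daily ratings and the ECBI-I. None of these three sections names therapist training, supervision or session feedback.

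**The concern.** A cost-effectiveness ratio should set the effect of a programme against the cost of producing that effect. Here the effect is produced by therapists who are trained, supervised weekly and given feedback. The cost is built from what each family consumes, and a training day, a supervision meeting and a tape review do not appear in any family's care record.

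The second objective of the trial depends on this ratio. The Discussion part of the Abstract and Ethics and dissemination both look ahead to use in practice if the training does better than CAU, without naming the support as a condition. The Background justifies the trial by a scarcity of certified therapists, so time from qualified supervisors may itself be scarce. A programme whose appeal is brevity could look cheaper than it is to run.

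**Working it through.** **1. What the rule captures.** Set against the counting units in Use of healthcare and Costs of healthcare:

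| Input (Study setting, Procedure) | Arises per | Caught by the records inventory or parent questionnaire |
|---|---|---|
| Training and booster sessions | family | yes, in minutes |
| Seven-hour training day | therapist | not named |
| Weekly supervision | therapist and week | not named |
| Feedback on taped first session | therapist | not named |

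The last three can enter only if the reference prices already contain them. The article does not say whether they do.

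**2. Direction.** The plan defines ICER = ΔC / ΔE. Let s_T and s_C be the support cost per family, beyond what the reference prices contain, for the brief training and for CAU. Then

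full-cost ICER − stated ICER = (s_T − s_C) / ΔE.

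With ΔE > 0 in favour of the training, the stated ICER is too low if s_T > s_C, unaffected if they are equal, and too high if s_C > s_T. The article documents programme-specific support for the training and none for CAU, so the likely direction is in favour of the training, but s_C is unreported. For a given cost gap, a smaller ΔE gives a larger shift; Sample size calculation plans for a small effect (d = 0.25).

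**3. Documented scale.** The plan gives no cost figure to reproduce. From Procedure, core contact is 120 + 120 + 60 = 300 min per family. From Study setting, the training day is 7 × 60 = 420 min per therapist. Ratio: 420 / 300 = 1.4 families' core contact per therapist trained.

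**4. Range under assumptions.** Planned size: 84 × 1.10 = 92.4, rounded up to 93, as stated in the plan. At 1:1 that is 93 / 2 = 46.5 families in the training arm, with core contact of 46.5 × 300 = 13,950 min = 232.5 h. Assumed, because not given: 5 to 30 therapists; 15 to 60 min of individual supervision per week; one family at a time; 3 to 6 weeks per family (Procedure allows up to six weeks for the three sessions).

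- Training day per family: 420 × 5 / 46.5 = 45 min, up to 420 × 30 / 46.5 = 271 min.
- Supervision per family, therapist time only: 15 × 3 = 45 min, up to 60 × 6 = 360 min.
- Sum: 45 + 45 = 90 min, up to 271 + 360 = 631 min.
- Against 300 min: 90 / 300 = 30%, up to 631 / 300 = 210%.

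Supervisor time and feedback time are left out and would raise these figures. Group supervision, several families at once, or spreading the training day over families treated after the trial would lower them.

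**5. The denominator.** Core contact is not the whole cost. Booster sessions of 60 min, at most every four weeks for a year, allow about 52 / 4 = 13 sessions, or 780 min. Against 300 + 780 = 1,080 min, the same range is 90 / 1,080 = 8% to 631 / 1,080 = 58%. The ICER also includes CAU after T1, education, justice and parents' productivity, for which no figures are given. The shift in the ICER therefore cannot be computed from the article.

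**The case against.** The strongest reply is that the rule treats both arms alike: used care times reference price, whoever gives it. Interventions says CAU may include longer parent training programmes, and the Background links such programmes to certified therapists. Any training or supervision behind that care is equally unnamed, so adding such costs to the brief training alone could bias the comparison the other way. This stands, and the remedy has to be two-sided.

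A second reply is that the reference prices may already carry supervision overhead, and that an article with one short paragraph on costs may leave such items to a fuller document. The first half stands: a reader might infer that these inputs cost nothing under the rule, and the article does not establish that. The second half carries less weight, because a counting unit and a valuation rule are stated, and followed as written they add no item for this support.

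Third, a reader might infer that the effect estimate is wrong or that the trial is not a test of effectiveness. The article does not support that. The support is openly part of how the training is delivered, so the effect does describe the programme as tested. Therapists have to be taught a new programme, and supervising them does not turn the study into an efficacy trial. What remains open is whether the effect carries over to delivery without the support, and the implementation statements are conditional in any case.

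Nor does the article show that CAU clinicians go unsupervised, or who employs or pays the supervisors.

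**Conclusion.** The point holds as a gap in the costing rule. Study setting makes the training day, weekly supervision and first-session feedback part of delivering the brief training, and the cost side of the ICER has no item for them. Unless the reference prices cover them, or CAU carries equal unpriced support, the ICER understates the relative cost of the training.

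The size is unknown. Only the 1.4 ratio is fully documented. The 30% to 210% range rests on assumed therapist numbers and supervision time and is relative to core contact, so it shows that the omission could matter but does not estimate the change in the ICER. It would be too much to conclude that the ICER is biased by construction, since that needs both the content of the reference prices and the support behind CAU. The cost-effectiveness objective is affected; the primary effect estimate, the sample size and the error rates are not.

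**What to change.** In Costs of healthcare, add programme-specific support as a cost item:

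- Count therapist and supervisor hours for weekly supervision and session feedback, and for the training day spread over the number of families a therapist would be expected to treat. Take them from logs, or reconstruct them. Vary the number of families per therapist in a sensitivity analysis.
- State what overhead the reference prices contain, and add only the excess, to avoid double counting.
- Apply the same rule to any comparable programme-specific training or supervision behind CAU, which means recording what CAU clinicians receive.
- Report the ICER with and without these items.

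In the Discussion part of the Abstract and in Ethics and dissemination, state that the effectiveness and cost-effectiveness conclusions apply to the training delivered with this supervision.

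The cost is some logging or reconstruction in both arms, a few sentences of text, and possibly a less favourable ICER. It is feasible: the article says costs are estimated only after families have finished, and the trial runs to December 2026. No change is needed to the sample size, randomisation or primary analysis.

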### Eligibility criteria

Families eligible for the trial must meet the following inclusion criteria:The child is aged between 2 and 12 years;Parents have to identify at least four behavioral difficulties of the child that occur in the home setting and that they want to target in the training, using an adapted version of a list of target behaviors [33, 36]. This list contains 29 behaviors that can be targeted in the training, such as hyperactive, impulsive, inattentive, oppositional and defiant behavior. The items are derived from target problems that parents mentioned in previous behavioral parent training groups and concern child behaviors that are commonly targeted in behavioral parent training in clinical practice, confirming ecological validity [36].

Exclusion criteria are:The child uses psychotropic medication (currently or in the month before the screening);The child has at any time received a diagnosis of autism spectrum disorder (ASD) in clinical practice, as (parents of) children with ASD may have different needs and therefore may require different treatments than children with behavioral difficulties without ASD;The child has a known IQ-score below 70, as (parents of) children with intellectual disabilities may have different needs and therefore may require different treatments than children with behavioral difficulties and typical intellectual abilities;Parents received behavioral parent training aimed at reducing the behavioral difficulties of the concerned child in the year prior to the start of the study;It is not a suitable period for the parents and/or the child to participate in the study (e.g., moving, divorce);The child is not living in the same household as the parent(s) who participate(s) in the trial during at least four weekdays (to ensure that our primary outcome can be reported by the same informant(s) and that parents can apply the intervention plans at home).

